### Secondary outcomes

Secondary outcomes will be analysed using generalized linear mixed-effects models. Data are measured repeatedly, but outcomes are binary or on ordinal scale. Crude and adjusted analysis will be presented. Covariates that will be adjusted for include age at OHCA, sex, educational level, and marital status. Continuous data will be analysed using *t*-test for normally distributed data and Wilcoxon’s signed-rank test for non-normally distributed data. For categorical data, chi-square test will be used.

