## Methods

### Trial design

The ROCK trial is a two-arm parallel group multicentre investigator-initiated pragmatic randomized controlled superiority trial with primary endpoint measured 12 months after the cardiac arrest.

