**Table 1 Tab1:**
[figure not shown]
SPIRIT figure. Schedule of enrolment, allocation, interventions, and assessments

*t*_1_ 2 weeks, *t*_2_ 6 weeks, *t*_3_ 12 weeks, *t*_4_ 26 weeks, *t*_x_ 52 weeks (primary endpoint). Readiness for return to work (*RRTW*), Multidimensional Fatigue Inventory (*MFI-20*), the 5-level EuroQol-5 domain (EQ-5D-5L) quality-of-life questionnaire, European quality-of-life survey (HeartQoL), the Pittsburgh Sleep Quality Index (PSQI), Health Literacy Questionnaire (HLQ), and Impact of Event Scale-Revised (IES-R). Intervention group only. Sequence analysis of labour market trajectories using data registered in the DREAM database. Only participants allocated to the intervention, §¤list of tests; Trail making A, Trail Making B, digit span forwards, digit span backwards, RBANS list learning, RBANS story memory, Rey’s complex figure test — copy, coding, Rey’s complex figure test, immediate recall, letter number sequencing, design fluency, RBANS list recall, RBANS list recognition, RBANS memory recall, block design, verbal fluency Test (animals), verbal fluency test (S-words)

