### Recruitment, assignment of interventions, sequence generation, and allocation concealment

We will recruit trial participants directly from the cardiology ward. A study nurse at the ward will approach eligible survivors and invite them to participate in the present study. Participants will be randomly assigned to either the intervention or the usual care group using a computer random generator, with a 1:1 allocation by using varying block sizes. The randomisation will be conducted using the RedCap randomization module and will be stratified on sex (M/F) and age. Allocation concealment will be ensured as the randomization module block sizes are unknown, and the allocation will be locked after randomization. Clinical staff at the departments will obtain informed consent and enroll the participants. A named study author ([name], [name], or [name]) will randomize participants, and the clinical staff at the departments will inform the participants about the allocation and start the intervention based on standard operating procedures. The CONSORT flow diagram is presented in Fig. 2.

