### Methods used for assumptions to be checked for statistical methods

In logistic regression, the linearity of log odds for each quantitative variable will be assessed by residual plots. Cooks distance and dfbeta values will be used to assess influential observations. In multistate models, the Markov assumption (previous states do not influence next transition) will be tested using the log-rank-based test [45].

The assumption of time homogeneity (that time spent in a state does not influence next transition) will be assessed using Schoenfeld residuals and by fitting a time homogeneity model and a piecewise constant model and comparing these using a likelihood ratio test. Repeated measures to identify the optimal covariance structure, models with compound symmetry, unstructured covariance, and auto-regressive with heterogeneous variance will be built and compared with ANOVA. The model with the lowest AIC and smallest −2 log likelihood score will be fitted as the final model. Time points should be equally spaced, as survivors fill surveys at approximate times during the study period. Normality will be assessed with a histogram of the residuals. Homoscedasticity will be assessed by plotting fitted values vs. residuals. Influential data points are not likely, as values are defined by surveys. The final model will be adjusted for values at baseline, to take individual variation into account.

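### Secondary outcomes: a paired test is named although the arms are independent, the covariance-selection rule can have no solution, and the equal-spacing statement does not match the visit schedule

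*Protocol article*

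**What the plan says.** The Protocol article describes a "two-arm parallel group multicentre investigator-initiated pragmatic randomized controlled superiority trial", with participants allocated "with a 1:1 allocation by using varying block sizes". No matching of participants is described.

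In the statistical section on secondary outcomes, the main analysis is set first: "Secondary outcomes will be analysed using generalized linear mixed-effects models". The text continues: "Data are measured repeatedly, but outcomes are binary or on ordinal scale". The same paragraph then gives continuous data a t-test if normal and otherwise Wilcoxon's "signed-rank test for non-normally distributed data", with chi-square for categorical data. Planned reporting again assigns the secondary variables to mixed models, apart from return to work at 6 months, which goes to logistic regression.

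The section on checking assumptions lists three covariance candidates for the repeated measures: compound symmetry, unstructured, and autoregressive with heterogeneous variance. The choice is "The model with the lowest AIC and smallest" −2 log likelihood, so both criteria are to be met. The same section states: "Time points should be equally spaced, as survivors fill surveys at approximate times during the study period". The note to Table 1 lists assessments at 2, 6, 12, 26 and 52 weeks.

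**The concern.** Three statements do not work as written.

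1. **The test.** Signed-rank is a one-sample or paired procedure. Between two independent arms it needs pairs that do not exist. If within-arm change was meant, the test is valid but says nothing about the treatment effect, and the chi-square test beside it does not suit paired data. The paragraph also does not say how these simple tests rank against the mixed model.

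2. **The selection rule.** Two of the three candidate structures are special cases of the third. A rule that demands the best value on a penalised and on an unpenalised criterion can leave no eligible model.

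3. **The spacing.** An autoregressive structure indexed by visit number gives every adjacent pair of visits the same correlation, whether the gap is 4 weeks or 26. That surveys are filled in at approximate times is no reason to treat them as evenly spaced.

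At stake are the secondary results, including health-related quality of life, which the Objectives name in the trial hypothesis. The primary outcome is analysed by logistic regression and is untouched.

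**Working it through.** The plan states no figure on this point, so there is none to reproduce.

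**Signed-rank test.** Inputs: unmatched 1:1 arms (Trial design; Recruitment and assignment section) and 85 per arm before dropout (Sample size). Illustration on assumed skewed (gamma) data, 85 per arm:

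- Re-pairing the two arms at random 1000 times moved the signed-rank p-value from 0.00015 to 0.035 on identical data. The rank-sum (Mann-Whitney) test gave one answer, 0.0020.
- With 85 and 83 per arm the paired test cannot be run. With an expected 20% dropout, unequal arms are likely.

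These figures show the nature of the error on assumed data. They are not properties of the plan.

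**Selection rule.** AIC = −2LL + 2q, where q is the number of covariance parameters and the mean model is held fixed. With five visits:

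- unstructured: q = 5×6/2 = 15
- heterogeneous AR: q = 5 + 1 = 6
- compound symmetry: q = 2

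Both simpler structures are unstructured with constraints, so unstructured always has the smallest −2LL. A simpler structure has the lower AIC when its −2LL exceeds that of unstructured by less than the penalty difference: 2×(15−6) = 18 for AR, 2×(15−2) = 26 for compound symmetry. In that case one model wins on AIC, another on −2LL, and none satisfies both.

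Simulation with 170 participants and five visits: when the true structure was compound symmetry (correlation 0.6) or AR by visit (0.7), AIC preferred a simpler structure in about 98% of runs. A shorter repeat of 150 runs each gave 99% and 96%. When correlation decayed with time (0.8 per 12 weeks), AIC chose unstructured and the rule gave an answer.

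**Spacing.** Gaps: 6−2 = 4, 12−6 = 6, 26−12 = 14, 52−26 = 26 weeks; 26/4 = 6.5. Assuming correlation 0.8 per 12 weeks, the correlation across a gap of g weeks is 0.8^(g/12):

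| Visits (weeks) | Gap (weeks) | Correlation |
|---|---|---|
| 2–6 | 4 | 0.93 |
| 6–12 | 6 | 0.89 |
| 12–26 | 14 | 0.77 |
| 26–52 | 26 | 0.62 |

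AR by visit number must use a single value for all four.

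**Consequence of the spacing error.** Each candidate was fitted to this true covariance by expected Gaussian likelihood, n = 170, constant variance:

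| Visits | Candidate | −2LL excess over unstructured | Penalty difference | Week-52 SD, fitted/true |
|---|---|---|---|---|
| 2, 6, 12, 26, 52 | heterogeneous AR | 97 | 18 | 1.22 |
| 2, 6, 12, 26, 52 | compound symmetry | 319 | 26 | – |
| 2, 26, 52 | heterogeneous AR | 0.2 | 4 | 1.005 |

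With complete data the standard error of the week-52 contrast is proportional to that SD, so AR would overstate it by about 22% with five visits. But 97 > 18 and 319 > 26, so AIC rejects both simpler structures. Assumed correlations of 0.6 to 0.9 per 12 weeks lead to the same choice.

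With weeks 2, 26 and 52 the gaps are 24 and 26 weeks and AR does no harm. There 0.2 < 4, so AIC would usually prefer AR while −2LL still prefers unstructured. The spacing statement is harmless in that case, but the two-criterion rule has no solution.

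**The case against.** The strongest reply is that this is loose wording around a sound main analysis. The paragraph does not say that the signed-rank test compares the arms. It opens with mixed models, Planned reporting repeats them, and no reporting slot for a signed-rank result is described, so the name is most plausibly a slip for rank-sum. The Table 1 grid is not shown, so five visits per questionnaire is unproven. The outcomes section describes collection within the first 12 weeks, then at 26 and 52 weeks, and an instrument used at weeks 2, 26 and 52 would be almost evenly spaced. If adjustment for baseline values leaves only weeks 26 and 52 as responses, there is one correlation and spacing does not matter. Two of the three candidates do not depend on spacing at all. A full analysis plan is still to be posted.

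Most of that stands and limits the size of the point. It does not rescue the three statements: the named test is wrong for independent arms, the selection rule can be empty, and the spacing statement disagrees with the listed schedule.

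Four stronger readings are tempting but unsupported:

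- **Natural recovery would be reported as a treatment effect.** A within-arm signed-rank test on an assumed 0.4 SD recovery, with 85 per arm and no arm effect, is significant in 85%, 95% and 99% of simulated trials for assumed pre-post correlations of 0.3, 0.5 and 0.6. This shows only that a paired test detects change; nothing in the article proposes to read it as a treatment effect.
- **The plan loses power by pairing arms arbitrarily.** A skewed example gives 68% against 78% for rank-sum, but the article proposes no such pairing.
- **All the repeated-measures models assume equal spacing, so the 52-week standard errors are wrong.** Only the AR candidate does, and with five visits AIC would reject it under the assumed decay.
- **The structure would be chosen to suit the result.** Allocation is masked as groups X and Y before analysis, which limits that risk, though it does not supply an answer when the rule has none.

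**Conclusion.** The concern holds as a correction to three statements about secondary outcomes, worth making before the analysis plan is final. The misnamed test and the two-criterion rule follow from the text and from nesting alone, without assumed data. The rule fails only when AIC prefers a structure simpler than unstructured, which depends on the true correlations and on the visits used.

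The spacing statement contradicts the full listed schedule, but its effect is confined to one candidate. Depending on visits, that candidate would overstate the week-52 standard error by between about 0.5% and 22%, and in the 22% case AIC would discard it. Those figures rest on an assumed correlation of 0.8 per 12 weeks, constant variance, Gaussian scores and 170 participants.

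**What to change.** - Replace signed-rank with the Wilcoxon rank-sum (Mann-Whitney) test. State that the mixed model is the governing between-arm analysis and that the t-test, rank-sum and chi-square tests are supportive only.
- Select the covariance structure by AIC alone, or prespecify unstructured. With five visits that is 15 parameters, which 170 to 214 participants can support.
- Delete the equal-spacing statement. State which visits each questionnaire contributes and, where they are unequally spaced, replace the AR candidate with a structure based on actual time in weeks (spatial power).

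The cost is a few lines of wording. The article says that a full analysis plan will be posted before analysis and that later changes will be registered and justified, so there is a place for them. Design, sample size and primary analysis do not change.

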### Methods used for assumptions to be checked for statistical methods

In logistic regression, the linearity of log odds for each quantitative variable will be assessed by residual plots. Cooks distance and dfbeta values will be used to assess influential observations. In multistate models, the Markov assumption (previous states do not influence next transition) will be tested using the log-rank-based test [45].

The assumption of time homogeneity (that time spent in a state does not influence next transition) will be assessed using Schoenfeld residuals and by fitting a time homogeneity model and a piecewise constant model and comparing these using a likelihood ratio test. Repeated measures to identify the optimal covariance structure, models with compound symmetry, unstructured covariance, and auto-regressive with heterogeneous variance will be built and compared with ANOVA. The model with the lowest AIC and smallest −2 log likelihood score will be fitted as the final model. Time points should be equally spaced, as survivors fill surveys at approximate times during the study period. Normality will be assessed with a histogram of the residuals. Homoscedasticity will be assessed by plotting fitted values vs. residuals. Influential data points are not likely, as values are defined by surveys. The final model will be adjusted for values at baseline, to take individual variation into account.

### Details of alternative methods to be used if distributional assumptions do not hold

In logistic regression, non-linear variables will be transformed or categorized to fulfil the assumption of linearity with log odds. In multistate models, if the Markov assumption is not fulfilled, a semi-Markov model (clock reset model) will be assessed, and time of entry into a previous or current state will be included as a time-dependent covariate (state arrival Markov model). If time homogeneity is not found, a piecewise constant model will be fitted. For repeated measures, non-normality or lack of homoscedasticity will be handled by log-transformation or categorizing variables or outcome.

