#### Impact of event scale-revised

The IES-R is a 22-item patient-reported outcome measure that assesses subjective distress caused by traumatic events [39]. The scale is rated on a 0 (not at all) to 4 (extremely) scale with respect to how distressing each item has been during the past week. Three subscales are formed and reflect intrusion (eight items), avoidance (eight items), and hyperarousal (six items).

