### Primary outcome

The primary outcome will be analysed using logistic regression assessing RTW status at 12 months adjusting for the intervention and age at OHCA, sex, marital status, and occupation prior to OHCA. Patient-reported data on return-to-work will be used to enrich the analysis (e.g. self-employed persons, activation of substantial self-regulated pensions, unemployed without social transfer payment).

Sequence analysis will visualize how survivors change states during the follow-up time [43, 44] but also describe time spent in each state (working vs. social transfer benefit, etc.) and order of states during follow-up. However, sequence analysis is exploratory and cannot answer hypotheses or be adjusted for covariates.

Because return to work is complex, transitions between work states will be explored further. Multistate models can be used to assess influences from covariates on transitions between stages, e.g. from working to social transfer benefit, or reverse, or from working until death.

Retirement is an important state in this setting; however, retirement to private pensions is not registered in the DREAM database [20]. Thus, a multistate model including this important state will have to be built using data from survivors’ questionnaires. This is possible, as retirement is an absorbing state see (Supplemental Figure 1).

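### For the repeated-measures secondary outcomes, a poor residual plot leads to logging or categorising the outcome, so the effect measure depends on the plot and categorising loses information

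*Protocol article*

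**What the plan says.** All places are in the protocol article.

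- **Trigger** (Methods used for assumptions to be checked for statistical methods). For repeated measures, "Normality will be assessed with a histogram of the residuals" and "Homoscedasticity will be assessed by plotting fitted values vs. residuals". For the logistic model, "the linearity of log odds for each quantitative variable will be assessed by residual plots".
- **Remedy** (Details of alternative methods to be used if distributional assumptions do not hold). For repeated measures, "non-normality or lack of homoscedasticity will be handled by log-transformation or categorizing variables or outcome". For the logistic model, "non-linear variables will be transformed or categorized to fulfil the assumption of linearity with log odds".
- **Planned model** (Secondary outcomes, within the statistical methods). Generalized linear mixed-effects models are used, and the repeated outcomes are described as binary or ordinal. Continuous data are mentioned separately, with simple two-group tests.
- **Reporting** (Planned reporting). Patient-reported measures are reported subscale by subscale.
- **A scale that reaches zero** (Impact of event scale-revised). "The scale is rated on a 0 (not at all) to 4 (extremely) scale".

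**The concern.** The remedy does not only repair a standard error. It replaces the quantity being estimated. A treatment effect on a raw score is a mean difference. After logging it is a ratio of geometric means, and after categorising it is an odds ratio. Which of these a reader gets for a given scale would be settled by an analyst's view of a plot of the trial data. Because each subscale is reported separately, subscales of one questionnaire could end up on different effect scales, hard to compare with each other or with other trials.

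Two further problems follow. Categorising discards within-category differences and so lowers power. And the checks suit a linear model with normal errors, whereas the article describes binary or ordinal outcomes. An outcome could be recoded to meet an assumption that the planned model does not make.

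**Working it through.** The plan gives no figure on this point, so there is none to reproduce. The check has four parts.

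**1. Does the trigger fit the planned model?** In a mixed model for a binary or ordinal outcome, residuals around the fitted value are not normal by construction, and the variance of a binary outcome changes with its mean, as p(1 − p). A residual histogram and a fitted-versus-residual plot would therefore show non-normality and unequal variance even when the model is right. Logging or further categorising does not answer that. If the checks are instead meant for scores analysed linearly, the text in Secondary outcomes does not describe that analysis. The two sections do not fit together either way.

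**2. Can the log be taken?** IES-R items are scored from 0 to 4. A participant who answers 0 to every item of a subscale scores 0, and ln(0) is undefined. Adding a constant first makes the result depend on the constant. With assumed constants of 1 and 0.5, the gap between scores of 0 and 4 becomes ln(5/1) = 1.61 or ln(4.5/0.5) = 2.20.

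**3. What does categorising cost?** Assumptions: a normally distributed outcome and a small shift between arms. The article gives no cut-points or number of categories, so a range is shown.

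For two groups cut at quantile q, with c the matching normal quantile and φ the normal density, the share of information kept is φ(c)² / [q(1 − q)]. To translate this into power, assume 80% power on the original scale at two-sided 5% (an assumption; the article makes no power claim for secondary outcomes). Power after the cut is Φ((1.960 + 0.842)·√share − 1.960).

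| Cut | Share kept | Power | N needed to recover |
|---|---|---|---|
| None | 1.00 | 80% | 1.00 × |
| Median | 0.637 (= 2/π) | 61% | 1/0.637 = 1.57 × |
| 70th percentile | 0.576 | 57% | 1/0.576 = 1.74 × |
| 80th percentile | 0.490 | 50% | 1/0.490 = 2.04 × |

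For k equal groups with boundaries e₀ to e_k, the share kept is k·Σ[φ(eᵢ₋₁) − φ(eᵢ)]².

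- k = 2: 0.637, a loss of 36%.
- k = 3: 0.793, a loss of 21%.
- k = 4: 0.861, a loss of 14%.

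Splitting into two groups is therefore the costly case. The median is the mildest two-group cut, and the loss shrinks as categories are added.

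**4. Is the primary analysis affected?** The primary outcome is already a dichotomy, so the outcome remedy cannot reach it. The primary model is fitted "adjusting for the intervention and age at OHCA, sex, marital status, and occupation prior to OHCA"; age is the only clearly quantitative covariate. In a simulation with 170 participants and an assumed non-linear age effect (1,500 trials), the average treatment odds ratio was 3.82 with age linear, 3.80 with age logged, 3.79 with a median split and 3.87 with thirds. Power was 0.87 in all four.

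**The case against.** The strongest reply is that details belong in the statistical analysis plan, which the article promises to post before analysis, and that groups are coded X and Y for the analyst. The trigger is a residual plot, not a p-value, so the form of the outcome is not chosen by result. Much of this stands. The absence of cut-points and trigger thresholds from an article is not a fault, and masking limits choice by favoured arm. A simulation under no effect illustrates the ceiling: free choice among four forms of a skewed outcome gave at least one significant result in 10.8% of trials, against 4.5% for the raw form. The plan does not allow selection on results, so that figure is not a prediction for this trial. But neither masking nor a later plan removes what the article itself states as the remedy. Even cut-points fixed in advance would change the effect measure and lose information.

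A second reply is that a mean difference is not clearly the planned measure, given the binary or ordinal description. That is right. It means that the starting effect measure is itself unclear, which strengthens the case for fixing it.

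A reader might also infer more than the documents support:

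- **That categorising age harms the primary analysis.** The treatment measure stays a conditional odds ratio and hardly moves. Randomisation is itself stratified on age, which would ordinarily use age bands, and the wording also allows a transformation.
- **That 170 participants would behave like 170 × 0.637 = 108.** This assumes a median split of a normal outcome, which the plan does not state, and 170 is the sample size for the primary outcome.
- **That cut-points will be picked after seeing the data.** The article is silent on this.
- **That logging discards information.** It does not; it changes the effect measure.
- **That the remedy will usually be needed.** The checks are on residuals, and the article gives no data on how these scales behave.

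**Conclusion.** The point holds for the repeated-measures secondary outcomes only, and it is minor. As written, a visual residual check can change the effect measure of a questionnaire scale. If the outcome is categorised, information is lost: about 36% for a median split of a normal outcome, more for an off-centre two-way cut (51% at the 80th percentile), and 21% or 14% with three or four equal groups. These sizes assume normality and categories that the article does not specify, so they show a range and are not a forecast. The failure of the log at 0 and the mismatch between the residual checks and the binary or ordinal description need no such assumptions; they follow from the text. The primary outcome is untouched.

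**What to change.** 1. In Details of alternative methods, delete the categorising of variables or outcome as a remedy for repeated measures.
2. State in advance, for each secondary outcome and subscale, the scale of analysis and the effect measure. If a log scale is wanted for any of them, declare it now, with the handling of zero scores.
3. Where a score is analysed on its own scale, keep that scale and handle poor residuals with robust (sandwich) confidence intervals, or bootstrap intervals that resample participants. Where an outcome is treated as ordinal, use an ordinal mixed model and drop the residual-normality check for it.
4. Align Secondary outcomes with the assumption checks, so that each check belongs to the model actually fitted.
5. Optional: enter age in the primary logistic model as a spline with knots set in advance (three knots cost one extra parameter). The expected effect on the treatment odds ratio is negligible.

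The cost is wording, plus sometimes slightly wider intervals; no new data are needed. The article anticipates the last visit on December 31, 2026 and says that changes will be registered and justified, so the change can be made in the registry record and the analysis plan before analysis.
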